**Fig. 1 Fig1:**
[figure not shown]
Flow of participants through the trial

### Sample size

A prospective sample size calculation has estimated that 306 participants (i.e. approximately 153 participants per group) are required to provide 80 % power to detect a clinically worthwhile difference of a 50 % reduction in injury in the intervention group (alpha set at 5 %). The sample size for the study was calculated assuming: (i) a combined incidence of injury of 30 % for medial tibial stress syndrome, patellofemoral pain, Achilles tendinopathy, and plantar fasciitis/plantar heel pain, and (ii) a drop-out of 20 %. The estimated incidence of lower limb injury was based on published data from studies investigating injury among Defence members completing basic training [2, 23, 24]. The drop-out rate for this trial was conservatively selected at the higher end of previous trials investigating the use of foot orthoses for the prevention of injuries in defence settings [25, 26], while also taking into account the completion rate of naval recruits undertaking the 11 weeks of basic training at HMAS Cerberus in the previous 12 months.

### Interventions

Interventions will be provided by experienced podiatrists who are professionally registered with the Podiatry Board of Australia. Prior to the study commencing, the assessors will attend a minimum of two training sessions. A detailed manual outlining study procedures will be provided to all assessors. The training sessions will be conducted by the chief investigator ([name]) who has 10 years of clinical and research experience using foot orthoses for musculoskeletal conditions.

Participants will be randomised to one of two groups: (i) a *control group* that will receive a pair of 3 mm flat insoles, or (ii) an *intervention group* that will receive a pair of Formthotics® prefabricated foot orthoses (Model: Original Single Medium) (Fig. 2). Both interventions, collectively referred to as shoe insoles, will: be manufactured by the same company (Foot Science International, Christchurch, New Zealand), be full-length insoles made from the same material (140 kg/m^3^ single density, closed cell polyethylene foam), and will have the same branding (i.e. company logo). The only difference between the two interventions will be the geometry and level of support that the shoe insoles provide (Fig. 2). To maintain blinding of participants, the participants will only be advised that they will receive one of two types of ‘shoe insole’ during the study. The allocated shoe insoles (flat insole or prefabricated foot orthosis) will be placed in the participant’s footwear and heat moulded to the participant’s feet and footwear. To achieve this, the participants will receive their footwear containing their heated insoles and they will be required to stand in them to enable the insoles to mould to their feet, as per the manufacturer’s instructions (Foot Science International, Christchurch, New Zealand). For the 3 mm flat insole, this moulding process will be one largely of slight compression of the material under weightbearing areas of the foot (i.e. it will not provide support to the arch of the foot or substantial contouring around the heel). Each participant will have their shoe insoles fitted to their athletic shoes and Defence-issued boots (i.e. two pairs of shoe insoles per participant) to maximise convenience and adherence to the interventions. All recruits will receive the same Defence-issued boots (Oliver Footwear Pty Ltd Structural Fire Fighter Boot, Model Number 20292) at the beginning of their 11 weeks of basic training (Fig. 3).

**Fig. 2 Fig2:**
[figure not shown]
The prefabricated foot orthosis (left) and flat insole (right) prior to being heat moulded to a participant’s foot. Top panels show lateral view, middle panels show posterior view and lower panels show medial view

**Fig. 3 Fig3:**
[figure not shown]
Oliver Footwear Pty Ltd Structural Fire Fighter Boot (Model Number:20292)

### Data collection sessions

Participants will attend three data collection sessions: baseline (session 1), week 2 (session 2) and week 11 (session 3).

#### Session 1 (baseline)

An initial assessment will be performed to determine the eligibility of participants. Injury history, general demographic data, physical assessments and anthropometric measures will be collected. This will include participants’ age, sex, waist and hip circumference, height and weight, foot posture [27], ankle joint dorsiflexion [28, 29], and a rating of lumbopelvic stability [30]. General health status will be determined using the Short-Form-12 Version 2 questionnaire [31] and physical activity (domestic, travel, work and recreation) in the previous four weeks will be measured using the Recent Physical Activity Questionnaire (RPAQ) [32]. Participants will also undergo a brief physical examination to determine if the clinical features used for the diagnosis of the four most expected lower limb injuries (Table 1) are present. Fitness information (e.g. multistage 20 m shuttle run test results) collected by Defence during the initial weeks of basic training will also be obtained for each participant.

**Table 1 Tab1:** Clinical features used for the diagnosis of the four most expected lower limb injuries

Injury	Clinical features
Medial tibial stress syndrome	Diffuse pain or oedema along the posteromedial border of the tibia;
	Pain spread over a minimum of 5 cm;
	Pain occurs with activity and lasts for at least a few hours post activity;
	Diffuse discomfort produced with palpation along the posteromedial border of the tibia, with discomfort confined to this region; and
	No history of paraesthesia.
Patellofemoral pain	Insidious onset of peripatellar or retropatellar knee pain;
	Pain on patellofemoral joint compression or resisted isometric quadriceps contraction at 30 degrees of knee flexion; and
	Peripatellar or retropatellar knee pain being provoked by at least two of the following activities: running, hopping, walking, marching, squatting, stair negotiation, prolonged sitting, or kneeling.
Achilles tendinopathy (midportion)	Insidious onset of pain located within 2 to 7 cm proximal to the insertion on the calcaneus; and
	Pain is reproducible with palpation of the Achilles tendon within 2 to 7 cm proximal to the insertion on the calcaneus; and
	Pain most noticeable after an extended period of rest and aggravated with activity.
Plantar fasciitis/plantar heel pain	Presence of pain in the plantar heel or medial arch;
	Pain is worse after rest but eases with mild activity;
	Pain is generally worse with prolonged standing or activity; and
	Pain is reproducible with palpation of the medial tuberosity of the calcaneus and/or along the plantar fascia.

Once all baseline measures have been taken, a therapist (separate investigator) located in an adjacent room (with no view of the participants) will allocate participants to one of the two groups (using the allocation system outlined in the manuscript). The therapist will fit and heat the allocated insoles into the participant’s footwear. Once the insoles have been heated, the therapist will place the participant’s footwear on a table outside of their room for the blinded assessor. The assessors, unaware of the insole allocation, will collect the participant’s footwear and advise the participants to wear their footwear for several minutes to allow moulding. Following this, participants will be asked to rate the comfort of their shoes after a brief period of wear (see the ‘outcome measures’ section for more detail). In addition, all participants will be issued with: (i) an information sheet informing them of the recommended wearing-in protocol and how to care for their shoe insoles, and (ii) an individual diary for participants to self-report pain levels over the 11 weeks of basic training. The self-report diaries will consist of body [33] and foot [34] pain drawings, which have been shown to have good to excellent inter- and intra-rater reliability of scoring the location of pain [33, 35]. Each week, participants will be required to indicate the presence and location of pain by shading within the outlines of the pain drawings. If pain is reported, participants will also be required to indicate the usual and worst pain experienced during the previous week on two separate 100 mm visual analogue scales (VAS) (see the ‘outcome measures’ section for more detail). At the completion of the initial assessment, participants will be invited to attend a review consultation the following week (session 2).

#### Session 2 (week 2)

At this session an assessor will be available to review all participants who are not finding their insoles comfortable. If participants report that the allocated insoles are uncomfortable, the insoles will initially be inspected to ensure that they fit the shoes and foot properly and will be re-moulded as per session 1. If adequate comfort is still not achieved, the section of the insole causing the discomfort will be identified and modified (either by spot heating or by grinding material away in the area of concern). The assessor will attempt to remove the least amount of material required to achieve comfort.

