#### Session 3 (week 11)

An exit interview will be conducted with an assessor that is blinded to group allocation in the final week of training (week 11). This session will be used to collect self-report diaries and confirm their accuracy and completeness with participants. In addition, if lower limb pain is being experienced by the participants at this session, the assessor will attempt to determine the presence of medial tibial stress syndrome [23], patellofemoral pain [36], Achilles tendinopathy [37], and plantar fasciitis/plantar heel pain [21, 38]. Finally, injury data will be cross-checked against ADF medical records.

All participants will remain blinded to their group allocation and will have a similar experience at all sessions regarding time spent with assessors, advice provided, and data collected. That is, the only difference between the groups will be the type of shoe insole received.

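### Session 2 gives insole modification to the assessor role that must be blind at week 11, and no rule keeps the two tasks apart for the same participant

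*Protocol article*

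**What the plan says.** All references are to the protocol article.

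- **Session 1 (baseline).** A therapist, who is a separate investigator working in an adjacent room, allocates participants and fits and heats the insoles. Assessors are kept apart from this: "The assessors, unaware of the insole allocation, will collect" the footwear once it is ready.
- **Session 2 (week 2).** The therapist is not mentioned. "At this session an assessor will be available to review all participants who are not finding their insoles comfortable". As a first step, "the insoles will initially be inspected to ensure that they fit the shoes and foot properly and will be re-moulded as per session 1". If that is not enough, "the section of the insole causing the discomfort will be identified and modified (either by spot heating or by grinding material away" at the point of concern. The person who does this is named: "The assessor will attempt to remove the least amount of material required to achieve comfort".
- **Interventions.** The two devices share material, maker and branding. "The only difference between the two interventions will be the geometry and level of support that the shoe insoles provide". The section adds that the flat insole, even after moulding, gives no arch support and little heel contour.
- **Session 3 (week 11).** "An exit interview will be conducted with an assessor that is blinded to group allocation". If the participant has lower limb pain at that visit, this assessor tries to establish whether any of the four target injuries is present.
- **Outcome measures.** The primary outcome draws on two sources: medical appointments and the assessors' findings at the exit interview.
- **Definition of injuries.** Assessors also score pain location from the diaries once these are handed in.
- **Evaluation of adherence.** A blinded assessor confirms adherence at session 3.

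**The concern.** The article takes care at baseline that the people who will judge outcomes do not handle the insoles. Two weeks later it gives the handling to that same role. A trained assessor who inspects a device, or grinds material off it, is likely to see whether it is flat or contoured.

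This matters because the exit diagnoses are clinical judgements. Under Table 1 they rest largely on history and palpation, and the Definition of injuries section calls the approach pragmatic because evidence on diagnostic accuracy is lacking. Judgements of that kind can be moved by knowing the allocation. The diary overlay scoring, which feeds the secondary outcome of overall lower limb pain, is done by the same role.

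The exposed participants are also not a random subset. They are the ones with insole discomfort. A contoured and a flat device may produce discomfort at different rates, and discomfort may be related to the pain that is later assessed. Any loss of blinding could therefore fall unevenly on the two arms.

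**Working it through.** The plan gives no figure on this point, and the sample size is not affected by it. The check is mainly a comparison of sections.

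**1. Who does what.**

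| Task | Role named | Blinding stated there |
|---|---|---|
| Allocate, fit and heat insoles (Session 1) | separate therapist | knows the allocation by function |
| Collect footwear, supervise moulding (Session 1) | assessor | yes, unaware |
| Review discomfort, remove material (Session 2) | assessor | none |
| Exit interview and diagnosis (Session 3) | assessor | yes, blinded |
| Confirm adherence (Evaluation of adherence) | assessor | yes, blinded |
| Score diary pain location (Definition of injuries) | assessor | none in that section |

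Inspection and re-moulding in session 2 are written in the passive. Re-moulding follows the session-1 procedure, in which the therapist did the heating. Removal of material is the step expressly given to the assessor.

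**2. Does handling reveal the group?** Geometry and support are the stated difference between the devices. The Discussion accepts that recruits living together may compare insoles and see that they differ. Someone trained in the study procedures who is reshaping the device is at least as well placed to tell.

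**3. Is there a separating rule?** Session 3 and Evaluation of adherence require the week-11 assessor to be blinded. No section says that session-2 assessors are different people, or that an assessor may not examine a participant whose insoles that assessor handled. Sessions 2 and 3 fit together only under such a rule.

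**4. Who is exposed?** For the primary outcome, all of the following must hold:
- the participant reports discomfort at week 2;
- the assessor sees or handles the insole (spot heating and grinding follow only if re-moulding fails);
- that same assessor conducts the participant's exit interview;
- the participant has lower limb pain at that visit;
- the diagnosis rests on the exit interview rather than on a medical appointment.

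An injury also requires worst pain of at least 30 mm on the participant's own scale, which the assessor does not set. For the diary outcome, it is enough that the assessor who handled the insole later scores that diary.

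**5. Can the size be given?** Suppose cases are missed in one arm only. At the planning incidence of 30% in Sample size, the fall in that arm's observed incidence is

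shift = 0.30 × f × e × q

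where f is the share of the arm's cases examined at exit by someone who had handled their insoles, e is the share of those cases that rest on the exit diagnosis, and q is the share of those misjudged because the group was known. The article gives none of the three. The values below are pure assumptions:

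- f = 0.1, e = 0.5, q = 0.1: 0.30 × 0.005 = 0.0015, or 0.15 percentage points
- f = 0.2, e = 0.5, q = 0.25: 0.30 × 0.025 = 0.0075, or 0.75 points
- f = 0.5, e = 0.5, q = 0.5: 0.30 × 0.125 = 0.0375, or 3.75 points

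The planned difference is 30% − 15% = 15 points, since a 50% reduction from 30% gives 15%. The assumed range runs from negligible to about a quarter of that difference (3.75 / 15 = 0.25). Nothing in the document favours one end. Over-diagnosis in the other arm is not covered by this formula and would add to the shift.

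**The case against.** The strongest reply is that the article already contains the rule. Session 3 makes blinding a condition of the exit interview, and Evaluation of adherence repeats it. Someone who has ground down an insole and recognised it does not meet that condition. Interventions refers to several assessors, so another could be used. It also refers to a detailed procedures manual, and a journal article commonly leaves rostering to such a manual. Session 2 does not call its assessor blinded, so there is no flat contradiction.

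Much of this stands. A reader might infer that the same person will do both tasks, or that assessor blinding is certain to fail. The document supports neither. It shows the risk for the role, not for any individual. Nor can the point be extended to session 1 because the assessor carries the fitted footwear: the article says these assessors are unaware of the allocation, and the insole is already inside the shoe.

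What does not stand is the suggestion that the article is simply silent. It describes the separate therapist at baseline in some detail and then names the assessor for the week-2 modification. That is stated staffing which works against the stated blinding, and the requirement at week 11 gives no means of securing it.

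**Conclusion.** The point holds in limited form. Session 2 assigns insole modification to the role that Session 1 shields from allocation and that later makes the exit diagnoses and scores the diaries. The article requires blinding at week 11, but no rule keeps an assessor off the exit interview or diary of a participant whose insoles that assessor handled.

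The exposure is confined to participants who report discomfort. For the primary outcome it is further confined to diagnoses made at the exit interview, since session 2 does not affect medical appointments. The conclusion assumes that a trained assessor handling the device can tell a flat insole from a contoured one, which follows from the stated difference in geometry.

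The size cannot be estimated from the document. A reader might infer a specific inflation of the false-positive rate, or a definite bias towards the orthosis. Neither follows, because the share of insoles adjusted, the overlap of staff and the effect of unblinding on diagnosis are all unknown. This is a cheap improvement to protect the blinding, not evidence that the trial's result would be wrong.

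**What to change.** Adopt one of two changes:

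- have the unblinded therapist role from session 1 carry out the session-2 inspection, re-moulding and modification; or
- keep assessors at session 2, and state that anyone who has handled a participant's insoles may not conduct that participant's week-11 assessment or score that participant's diary.

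Trial status says that recruitment began in January 2015, so session 2 may already have run for some cohorts. For those, record who handled each insole and add a sensitivity analysis that excludes exit diagnoses made by those staff for those participants.

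The cost is rostering at weeks 2 and 11 and a sentence in the protocol. The first option has a further drawback: Session 1 places the therapist where participants cannot be seen, and using that role at week 2 would bring unblinded staff into some contact with participants. The article does not say how many therapists or assessors there are, so whether extra staff time is needed cannot be judged from it. The second option avoids that contact, but it needs a handling log and enough assessors to rotate.

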#### Session 3 (week 11)

An exit interview will be conducted with an assessor that is blinded to group allocation in the final week of training (week 11). This session will be used to collect self-report diaries and confirm their accuracy and completeness with participants. In addition, if lower limb pain is being experienced by the participants at this session, the assessor will attempt to determine the presence of medial tibial stress syndrome [23], patellofemoral pain [36], Achilles tendinopathy [37], and plantar fasciitis/plantar heel pain [21, 38]. Finally, injury data will be cross-checked against ADF medical records.

All participants will remain blinded to their group allocation and will have a similar experience at all sessions regarding time spent with assessors, advice provided, and data collected. That is, the only difference between the groups will be the type of shoe insole received.

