### Definition of injuries

For the purpose of this trial, an injury will be defined by the presence of pain that scores at least 30 mm on a 100 mm visual analogue scale when at its worst [21, 22]. Due to the lack of evidence regarding the diagnostic accuracy of the lower limb injuries of interest, the diagnosis of medial tibial stress syndrome [23], patellofemoral pain [36], Achilles tendinopathy [37], and plantar fasciitis/plantar heel pain [21] will be determined using a pragmatic approach via clinical assessments based on definitions described in previous studies (Table 1).

Over the 11 weeks of basic training, participants will document the presence and location of pain on pain drawings in their weekly self-report diaries. The pain drawings will identify the presence and location of pain in the body or feet, but they will not provide a specific diagnosis regarding the cause of pain. Once the self-report diaries have been submitted at the exit interview, the assessors will use a transparent overlay divided into multiple body areas to determine pain location.

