### Outcome measures

The *primary outcome measure* will be the combined incidence of the four common lower limb injuries (medial tibial stress syndrome, patellofemoral pain, Achilles tendinopathy, and plantar fasciitis/plantar heel pain) as determined at medical appointments and by assessors at the exit interview (week 11).

*Secondary outcomes* include:(i)the overall incidence of lower limb pain as determined by pain drawings in self-report diaries, measured at week 11;(ii)the severity (usual and worst) of over-use lower limb pain as determined by the 100 mm VAS in self-report diaries, measured at week 11;(iii)the time (in days) to lower limb injury and pain as determined by self-report diaries and navy medical records, measured at weeks 1 to 11;(iv)time to drop-out from injury (in days) as determined by navy administration records, measured at weeks 1 to 11;(v)the type, frequency and severity (mild, moderate or severe) of self-reported adverse events (such as new pains, shoe/insole discomfort and blisters) will be obtained from the self-report diaries, measured at weeks 1 to 11;(vi)lost training days as determined by navy administration and medical records, measured at weeks 1 to 11;(vii)shoe comfort will be measured using a 100 mm visual analogue scale, measured at baseline and week 11;(viii)general health status will be determined using the Short-Form-12 (SF-12) Version 2 questionnaire [31], measured at baseline and week 11.

Shoe comfort will be determined using a 100 mm visual analogue scale, which has been shown to have good reliability [39]. The left end of the scale (0 mm) is labelled “not comfortable at all” and the right end of the scale (100 mm) is labelled “most comfortable imaginable”. Participants will be instructed to place a mark on the scale that represents their perceived comfort rating. Similarly, pain will be determined using a 100 mm visual analogue scale. To indicate the range of pain to participants, the left end of the scale (0 mm) is labelled “no pain” and the right end of the scale (100 mm) is labelled “worst pain imaginable”. The VAS has been shown to be a valid [40] and reliable [39] measure of pain.

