### Statistical analysis

Statistical analysis will be performed using SPSS version 22.0 or later (SPSS Corp, Chicago, Ill, USA) using the intention-to-treat principle, where all randomised participants will be included in the final analyses. The endpoint will be the completion of the 11 weeks of basic training for each participant. Multiple imputation will be used to replace any missing data using five iterations, with age, and group allocation as predictors [43]. The exception will be for the variable adverse events where no data substitution will be applied.

Participant characteristics and baseline data will be summarised by descriptive statistics. Distribution of continuous variables will be checked for normality and transformation will be carried out if necessary prior to the use of parametric statistics. Outcome data will be analysed according to a pre-planned protocol. Differences in the primary and secondary outcome measures between the two groups will be compared.

The differences between groups for the primary outcome measure of the combined incidence of the four common lower limb injuries (medial tibial stress syndrome, patellofemoral pain, Achilles tendinopathy, and plantar fasciitis/plantar heel pain) and the secondary outcome measure of the incidence of lower limb pain (overall and body region specific) during the 11 week training period will be compared using incidence rate ratios.

In regard to the other secondary outcomes, differences between groups for continuous outcome measures (severity of pain, lost training days and shoe comfort) will be analysed using independent t-tests. The time to lower limb injury and pain and drop-out will be compared using Cox proportional hazards ratios. Adherence of the shoe insole interventions will also be analysed using independent *t*-tests. The difference between groups for the outcome measure of health status (SF-12) will be compared using analysis of covariance (ANCOVA) with baseline scores and intervention group entered as independent variables [44].

95 % confidence intervals will also be provided to indicate precision of point estimates. We will also conduct hypothesis tests where appropriate, which will be considered significant if *p* < 0.05. Effect sizes will be determined using standardised mean differences (Cohen’s *d*) for continuous data.

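### The primary outcome is analysed as 11-week incidence, but injuries never taken to a medical appointment count only if painful on the exit day

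*Protocol article*

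**What the plan says.** All places are in the Protocol article.

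- **Period.** Under Statistical analysis, the incidence of the four injuries "during the 11 week training period will be compared using incidence rate ratios".
- **Routes to a case.** Under Outcome measures, the primary outcome is the combined incidence "as determined at medical appointments and by assessors at the exit interview (week 11"). No third route is named.
- **Condition at exit.** Under Session 3 (week 11), the four diagnoses are sought "if lower limb pain is being experienced by the participants at this session, the assessor will attempt to determine the presence" of each.
- **Injury definition.** Under Definition of injuries, "an injury will be defined by the presence of pain that scores at least" 30 mm on the 100 mm scale when at its worst, with no restriction to the exit day. The diagnoses themselves "will be determined using a pragmatic approach via clinical assessments based on definitions described in previous studies (Table 1").
- **Diaries.** The same section says of the pain drawings that "they will not provide a specific diagnosis regarding the cause of pain".
- **Other contacts.** Session 3 adds that "injury data will be cross-checked against ADF medical records". At Session 2, "an assessor will be available to review all participants who are not finding their insoles comfortable"; no injury diagnosis is described there.

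**The concern.** The named outcome and the way cases are found do not match. Consider a recruit whose diary shows several weeks of shin pain at 50 mm, who does not report it to medical staff and is free of pain at week 11. That recruit meets the pain threshold in the injury definition, yet is a non-case for the primary outcome.

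Two things are at stake. First, fewer events are counted than occurred, which costs power if the planning rate assumed that all were counted. Second, the outcome combines the occurrence of injury with its duration and with the decision to seek care. The Background says that foot orthoses benefit the treatment of several lower limb disorders, so an effect on duration is plausible on the document's own account. The trial's conclusion is to be about prevention, and this outcome alone cannot separate prevention from faster recovery.

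**Working it through.** **1. Is there another way in for an unpresented, resolved injury?**

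- Medical appointments: no, because by assumption it was never presented.
- Exit interview: no, because no pain is present that day.
- Cross-check with medical records: no, because they cannot hold an injury that was never presented.
- Session 2: no, it is a comfort review.
- Diaries: they hold location and severity by week, and the assessor confirms them at exit, but no rule turns a past episode into one of the four diagnoses.

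Such an injury is absent from the primary outcome. Its pain still enters secondary outcome (i), incidence of lower limb pain, and (iii), time to injury and pain.

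**2. Reproduce the planned sample size.**

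Inputs from Sample size: 30% against 15% (a 50% reduction), power 80%, alpha 5% (taken as two-sided; not stated), drop-out 20%, total 306.

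n per arm = [1.960·√(2p̄(1−p̄)) + 0.842·√(p₁(1−p₁) + p₂(1−p₂))]² / (p₁−p₂)², with p̄ = 0.225

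= (1.157 + 0.489)² / 0.15² = 120.5, so 121. Then 121/0.8 = 151.25, so 152 per arm and 304 in total. This agrees with 306 to within two participants.

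**3. Power when cases are missed equally in both arms.**

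Evaluable per arm: 153 × 0.8 = 122.4, taken as 122.

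Power = Φ{[(p₁−p₂)·√n − 1.960·√(2p̄(1−p̄))] / √(p₁(1−p₁) + p₂(1−p₂))}

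With a share m missed, p₁ = 0.30(1−m) and p₂ = 0.15(1−m). For m = 0.20: (0.12 × √122 − 1.065)/0.537 = (1.325 − 1.065)/0.537 = 0.485, and Φ(0.485) = 0.686.

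| Share missed (assumed) | Control v intervention | Ratio | Power at 122 per arm | Total N for 80% power, 20% drop-out |
|---|---|---|---|---|
| 0% | 30% v 15% | 0.50 | 80.5% | 304 |
| 20% | 24% v 12% | 0.50 | 68.6% | 400 |
| 30% | 21% v 10.5% | 0.50 | 61.6% | 470 |
| 40% | 18% v 9% | 0.50 | 53.9% | 566 |

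**4. The ratio when the arms differ in what is missed (assumed shares).**

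- 30% missed in control, 20% in intervention: (0.15 × 0.80)/(0.30 × 0.70) = 0.12/0.21 = 0.57.
- 20% in control, 30% in intervention: 0.105/0.24 = 0.44.
- No preventive effect at all (30% in both arms), 30% missed in control and 40% in intervention: 0.18/0.21 = 0.86.

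The last line is the one that matters for the conclusion: a pure effect on recovery or care seeking would show as a 14% reduction in incidence.

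**The case against.** **The exit condition has a rationale.** Each of the four injuries in Table 1 requires an examination finding: palpation, or patellofemoral compression or resisted contraction. A resolved episode cannot show one. Requiring an examined diagnosis gives up sensitivity for specificity, which is a defensible choice. Making history-only diagnoses part of the primary outcome could also do harm, because false positives pull the ratio towards 1. With perfect sensitivity and 95% specificity (assumed), the rates become 0.30 + 0.70 × 0.05 = 33.5% and 0.15 + 0.85 × 0.05 = 19.25%, a ratio of 0.57 with power 72%. At 90% specificity they are 37% and 23.5%, a ratio of 0.64 with power 63%. This stands, and it is why the fix does not replace the primary outcome.

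**The power loss is conditional.** The 30% comes from published studies of basic training, and the article does not say how they found cases. If they had similar gaps, the loss is smaller or absent. This stands.

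**No bias between arms is shown.** Equal misses leave the ratio at 0.50. Participants and assessors are blinded, and the Discussion describes access to medical care as largely standardised. This stands as to proof. Blinding does not, however, stop a device from changing how long pain lasts.

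**Stronger readings that the document does not support.** A reader might infer that clinic diagnoses are exempt from the 30 mm rule or from Table 1. Definition of injuries sets both for the trial as a whole; how they are applied to medical appointments is simply not described in the article. A reader might also infer that these injuries are lost to the trial altogether. They are lost to the primary outcome only.

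**Conclusion.** The mismatch holds on the text. For recruits who never attend a medical appointment, an outcome named and analysed as incidence over 11 weeks is a point prevalence at week 11. How many injuries this affects is unknown. On the two assumptions that 30% is a full-capture rate and that 20% to 40% of cases are missed equally, power falls from about 80% to between 69% and 54%, with no bias in the ratio. Bias needs the insole to alter recovery or care seeking; the document makes the former plausible but gives no figure for either. The point does not invalidate the design. It limits how far a difference in the primary outcome can be read as prevention, and it should be addressed.

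**What to change.** Reconcile the text under Session 3 (week 11), Definition of injuries and Outcome measures as follows.

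1. **Data collection.** Remove the condition of pain at the session. At exit, the blinded assessor reviews every diary week with lower limb pain of at least 30 mm at worst. Each episode is classified by the site overlay and the history features of Table 1, with examination if it is still painful, and labelled current or resolved.
2. **Primary outcome.** Keep the presented-or-examined definition, and describe it as injuries diagnosed at medical appointments or present at week 11.
3. **Sensitivity analysis.** Pre-specify one that adds the resolved episodes. If the two analyses disagree, limit the conclusion about prevention accordingly.

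**Cost.** A few minutes per exit interview, with existing assessors and diaries. Resolved episodes lack palpation and may include false positives. The diary is described as having one usual-pain and one worst-pain scale per week, so where several sites are shaded the 30 mm may belong to another site. Recruitment began in January 2015, so recruits who have already exited can be classified from their diaries only.
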